### Intervention

Participants will be randomly assigned to receive either G4H or CBT. Groups will not commence unless a minimum of 5 people have consented to participate, with the maximum number of people recruited to each group being 9 people. Interventions are matched for contact time and mode of delivery, and both include five group sessions of 60–90 min in duration, run weekly for the first four weeks, and a final “booster” session that is held one month later. Postgraduate students in professional psychology (with provisional registration) will facilitate the groups (2 facilitators per group). Treatment fidelity and consistency of program delivery will be maintained by providing: a half-day of training, weekly group supervision from a registered clinical psychologist, direct observation by investigators to ensure quality, and regular team meetings with the research team. Additionally, G4H facilitators will anonymously complete a brief questionnaire at the end of each session to assess (a) what session activities were covered, (b) the length of session, and (c) facilitator session satisfaction and ease of delivery. Facilitators will also record participant attendance.

#### Groups 4 health (G4H)

G4H is a manualised, five-session group-based intervention designed to reduce loneliness through facilitating social group integration [21, 22]. The program is comprised of five modules — the contents of which are summarised in Fig. 1 below.

**Fig. 1 Fig1:**
[figure not shown]
Overview of the Groups 4 Health Modules

##### Module 1: Schooling

This module seeks to raise awareness of the beneficial effects that social group memberships have for health. Module 1 highlights the costs of ignoring the social dimensions of health and points out that using all of the social resources at our disposal generally leads to optimal health outcomes. The module also emphasises people’s power to counter these effects by learning how best to develop, maintain and harness group-based resources.

##### Module 2: Scoping

Explores each person’s current group-based resources. This module engages participants in the process of *social identity mapping* [25]. This tool was developed to explore respondents’ social identities in a way that is engaging, visual, and concrete. The map is then used to facilitate a discussion of how people would ideally like their groups to look in the future and identify any gaps in group networks.

##### Module 3: Sourcing

Targets development of strategies needed to identify and strengthen existing valued social identities. The goal of Module 3 is to assist people to optimize and sustain their group memberships over the long term. Participants develop solutions to barriers to making the most of existing groups.

##### Module 4: Scaffolding

Uses the G4H group as an exemplar for developing and embedding new social group connections, whilst also identifying which connections to develop. Group members are facilitated to prepare a social plan of action. These social plans are then trialled between this and the final module, which takes place one month later.

##### Module 5: Sustaining

Is a booster session, held one month after Module 4 that seeks to troubleshoot any problems that people have encountered in implementing their social plans. Module 5 also revisits social identity maps, created in Module 2, to see how they have changed over the course of the program. The skills that have been learned across the previous modules are reviewed and key messages reinforced with the goal of encouraging long-term maintenance.

The program is supported by a facilitator manual and client workbook. The workbook contains a summary of the key learnings for each session, with sufficient space to complete activities (both within the sessions and as homework) and document any relevant notes and plans to achieve a person’s individual goals.

#### Group cognitive behaviour therapy

The active comparison condition will involve the delivery of the current best-practice intervention for the treatment of adolescent depression: CBT. Specifically, an existing brief manualised program for group-based CBT for depression [27] will be used with minor adaptations to ensure comparable structure and amount of face-to-face contact as the G4H condition. This specific manualised version of CBT has been found to be effective in reducing depression symptoms in a sample of high-risk adolescents relative to active control groups (*N* = 341; [28]). Indeed, a meta-analysis found that this particular manualised program showed greater effect sizes than similar interventions with longer duration [29].

The manualised program involves the following components: (1) psychoeducation, in which participants learn about the link between thoughts, mood, and behaviour; (2) behavioural activation, in which participants learn strategies to increase activities that boost their sense of pleasure and achievement; and (3) cognitive restructuring, in which participants learn strategies for challenging and reframing unhelpful thinking patterns that maintain depression. The program also includes homework tasks and group-based activities.

### Measures

Each participant will be asked to complete online surveys (or paper-and-pencil if they prefer) at eight time points. The full questionnaire package measuring all outcomes of interest will be administered before the intervention (T0), on its completion (T5), 6 months later (T6) and 12 months later (T7) – see Table 1 for a summary. These should take about 10–20 min on each occasion. In addition, a brief one-page questionnaire will be administered at the end of each session (T1, T2, T3, and T4), which will (only) include measures of depression symptoms, loneliness, module feedback, and group identification.

**Table 1 Tab1:** Overview of CARR measures and timepoints of measurement

Construct	Measure	T0 Baseline	T1 After session 1	T2 After session 2	T3 After session 3	T4 After session 4	T5 Post-treatment	T6 6-month follow up	T7 12-month follow up
Primary outcomes	Depression (DASS-21)	•	•	•	•	•	•	•	•
	Depression (PHQ-9)	•					•	•	•
	Loneliness (4 item)	•	•	•	•	•	•	•	•
	Loneliness (20 item)	•					•	•	•
Secondary outcomes	Social anxiety	•					•	•	•
	GP attendance (last month)	•					•	•	•
	Wellbeing	•					•	•	•
	Life satisfaction	•					•	•	•
	Self esteem	•					•	•	•
	Subjective physical health	•					•	•	•
Process measures	Multiple group membership	•					•	•	•
	Multiple group compatibility	•					•	•	•
	Mental illness identity	•					•	•	•
	Group cohesion						•		
	Therapy group identification		•	•	•	•	•		
	Service identification						•		
Acceptability/feasibility	Useful		•	•	•	•	•	•	•
	Enjoyed						•	•	•
	Interesting						•	•	•
	Learnt something						•	•	•
	Homework completion		•	•	•	•	•		
	Facilitator questionnaire		•	•	•	•	•		
	Attendance		•	•	•	•	•		

Notes: *DASS21* Depression Anxiety Stress Scales (21 item)

*PHQ-9* Patient Health Questionnaire (9 item).

*GP* General Practitioner

### Primary outcomes

*Depression, Anxiety and Stress Scale* [30]*.* This measure comprises 21 items, 7 for each construct, for example “I felt that life was meaningless”, rated on a 4-point scale (0 = did not apply to me at all, 3 = applied to me very much, or most of the time. It has been validated for use with adolescents as young as 11 years in Australia [31], with an improvement greater than 3 points considered clinically significant [32]. The full DASS-21 (including anxiety and stress subscales) will be administered at T0, T5, T6 and T7, while the depression subscale will be administered at all timepoints T0-T7. The 9-item Patient Health Questionnaire is included as an additional measure of depression (T0, T5, T6, T7); this will be used as a screening tool rather than as the primary outcome measure.

*UCLA-20:* The UCLA Loneliness scale has been validated for use with a young adult sample [33, 34]. It comprises 20 items, for example “Felt isolated from others” requiring a response on a 4-point scale (1 = never, 4 = often). The full scale will be included at T0, T5, T6 and T7, and a 4-item version of the UCLA scale will be included in the end of session questionnaire (T1-T4).

### Secondary outcomes

#### Social anxiety

This was assessed with the Social Phobia Inventory (SPIN; [35]), comprising 17 items (e.g., “Being embarrassed or looking stupid are among my worst fears”). Each item is rated on a 5-point scale (1 = not at all, 5 = extremely), with higher scores indicating greater social anxiety.

#### General practitioner (GP) visits

This was measured with a single item: “How many times have you been to see a general practitioner (medical doctor) in the last month” (as used in [25, 36]).

#### Subjective wellbeing

The Short Warwick Edinburgh Mental Wellbeing Scale [37] will be used to index well-being. It is a 7 item scale with positively worded items (e.g., “I’ve been thinking clearly”), which respondents rate for how often they have experienced them over the past two weeks, on a 5-point scale (1 = none of the time; to 5 = all of the time).

#### Life satisfaction

The Satisfaction With Life Scale (SWLS; [38]) will be included to assess global life satisfaction. Participants will respond to 5 items (e.g., “I am satisfied with my life”) on a 7-point scale (1 = strongly disagree, 7-strongly agree).

#### Self esteem

This was measured using the Single Item Self Esteem measure (SISE; [39]). Participants responded to the item “I have high self esteem” on a 4-point scale (1 = not at all true of me, 4 = very true of me).

#### Subjective physical health

Participant’s self-rated health status was measured using a single item “My current overall health is…”, with responses ranging from 1 (very poor) to 7 (very good). This measure is widely used in community and population health studies and has been found to be a valid predictor of physical health and mortality risk [40].

### Process measures

Five measures will be used to index different aspects of social identification and group processes as follows:(i).*Social identification with treatment group:* This is a 4-item scale [41] was used to assess identification with the treatment group (e.g., “I identify with my G4H group/CBT group”) and is rated on a 7-point scale (1 = strongly disagree, 7 = strongly agree).(ii).*Social identification with service:* This is a 4-item scale [41] was used to assess identification with the service (e.g., “I identify with Headspace/the UQ Psychology Clinic”) and is rated on the same 7-point scale used above (1 = strongly disagree, 7 = strongly agree).(iii).*Multiple group membership.* This will be measured using the Multiple Group Membership scale from the Exeter Identity and Transition Scales [42]. The 3-item version of the scale was used to index people’s strength of connectedness to multiple groups [43]. Participants are asked to rate each item (e.g., “I am a member of lots of different social groups”) on a 5-point scale (1 = do not agree at all, 5 = agree completely).(iv).*Social identity centrality:* This is a 7-item scale adapted from [44] assessing the psychological salience of a particular social category membership, here as someone with mental health problems (e.g., “I often think about the fact that I am a person who has problems with mental health”; 1 = do not agree at all, 5 = agree completely).(v).*Group Cohesion.* The Group Environment Scale – Cohesion subscale [45] will be used to measure treatment group cohesion. Nine items (e.g., “There is a strong feeling of belongingness in this group”) are measured on a 7-point scale (1 = not at all, 7 = very much).

### Acceptability and feasibility

Participants will be asked to rate their perceived usefulness of the program after every session (T1-T5): “How useful did you find today’s module?” on a scale from 1 (not useful at all) to 10 (very useful). At T5, T6, and T7, participants will additionally be asked to rate how much they enjoyed the program, found the program interesting, learnt from the program, and how likely they were to use the techniques they learned during the program (each on a 1–10 scale). Facilitators will also provide a rating of the perceived usefulness, relevance, learning, and enjoyment for participants after each module (T1-T5).

Qualitative feedback on the program will be sought from participants and facilitators, both in the form of written feedback (at T1-T7) as well as in a series of focus groups conducted separately with a subgroup of participants (including those who withdrew from the program) and facilitators.

### Sample size power calculations

The CARR sample size was determined by power calculations for a non-inferiority trial, using effect sizes and retention rates from our published pilot study. We have estimated the non-inferiority margin based on historical evidence for the effect size of the active comparator (based on recommendations by [46] and [47]). The effect size of this CBT program versus control was *d* = 0.49 at 6 month follow up (recalculated from [28] using methods recommended by [19]). This corresponds to 2.2 points on the DASS-21 depression subscale (using the expected standard deviation for an adolescent population of 4.53; [31]). To have 0.80 power to detect this difference with an alpha level of 0.05*,* 67 people per condition would need to be retained at follow up. Assuming 50% eligibility and 67% survival rates, which are consistent with our pilot data, we anticipate that screening 400 people for eligibility (see Fig. 2) will lead to retention of *N* = 67 per condition at follow up [48]. However, this is a conservative estimate of retention due to the addition of incentives for follow up data completion in this trial [49].

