H1 will be considered supported if there is evidence of significant improvements in loneliness in the G4H condition (H1a), and a significant condition by time interaction, such that improvements in loneliness over time will be greater for the G4H condition than in the CBT condition (H1b). H2 will be considered supported if there is evidence of significant improvements in depression in both conditions, with a non-significant condition by time interaction. The non-inferiority margin will be a DASS-21 depression change score difference of 2.20. H3 will be considered supported if there is no significant increase in depression and loneliness scores between T6 and T7 in the G4H condition.

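### The non-inferiority margin of 2.20 is essentially the whole estimated CBT-versus-control effect, so meeting it cannot show that G4H is as effective as CBT

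*Protocol article*

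**What the plan says.** The section on sample size power calculations gives the source of the margin: "We have estimated the non-inferiority margin based on historical evidence for the effect size of the active comparator". It then gives the effect, "The effect size of this CBT program versus control was *d* = 0.49 at 6 month follow up", and converts it to scale points, "using the expected standard deviation for an adolescent population of 4.53": "This corresponds to 2.2 points on the DASS-21 depression subscale". The same figure drives the sample size, "To have 0.80 power to detect this difference with an alpha level of 0.05", which leads to 67 retained per condition. The Analyses section fixes the value: "The non-inferiority margin will be a DASS-21 depression change score difference of 2.20".

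The article states no preserved fraction, no confidence limit for the historical effect, and no clinical reason for accepting a loss of 2.2 points. It cites two sets of recommendations for the approach but reports nothing from them beyond the use of the historical effect.

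H2 (Aims) is worded as G4H being as effective as CBT on depression at program completion. The Analyses section counts H2 as supported if both conditions improve significantly and the condition by time interaction is non-significant. The margin is stated straight afterwards, but no confidence limit is compared with it.

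**The concern.** A margin derived from the comparator's effect has to be smaller than that effect if meeting it is to mean that the comparator's benefit has been substantially kept. Here the two are the same number. A pass would then bear on whether G4H beats the historical control, an indirect and weaker question than the one H2 asks.

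The estimate of 0.49 is also used as if it were known. If CBT's true effect is smaller, a treatment no better than that study's control lies inside the margin. At stake is the trial's main non-inferiority conclusion: a positive H2 would be reported as parity with CBT on evidence that cannot carry that claim.

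**Working it through.** **Inputs (protocol article).** d = 0.49, SD 4.53, power 0.80, alpha 0.05, 67 per condition and 67% retention (Sample size power calculations); margin 2.20 (Analyses); N = 341 for the trial of this CBT program (Group cognitive behaviour therapy). **Assumption:** the article does not give that trial's arm sizes, so two to four equal arms without attrition are used. Clustering by therapy group is ignored throughout.

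1. **Reproduce the stated n.** n = 2(1.96 + 0.8416)² × 4.53² / 2.2² = 2 × 7.849 × 20.52 / 4.84 = 66.6, rounded up to 67. This matches the article, with a true difference of zero and two-sided 0.05 (one-sided 0.025). One-sided 0.05 gives 53. The full 2.2 points were therefore used, with no discount.

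2. **Share of the effect preserved.** 0.49 × 4.53 = 2.22, and 2.20 / 2.22 = 0.99. A deficit at the margin leaves 2.22 − 2.20 = 0.02 points, about 1% of the estimated benefit.

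3. **Sampling error of the historical effect.** SE(d) = √(2/n + d²/(4n)); lower limit = 0.49 − 1.96 × SE(d); points = limit × 4.53.

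| Assumed arms | n per arm | Lower limit (d) | In points | 2.20 / limit |
|---|---|---|---|---|
| 2 | 170 | 0.27 | 1.24 | 1.8 |
| 3 | 114 | 0.23 | 1.03 | 2.1 |
| 4 | 85 | 0.18 | 0.84 | 2.6 |

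4. **What a confidence-limit rule at 2.20 would do.** SE of the difference = 4.53 × √(2/67) = 0.783. An upper limit below 2.20 requires an observed deficit below 2.20 − 1.96 × 0.783 = 0.67 points. Suppose G4H is exactly as good as the historical control, so that its true deficit equals the true CBT effect Δ. The chance of passing is Φ((2.20 − Δ)/0.783 − 1.96):
   - Δ = 2.22 (estimate exact): Φ(−1.99), about 2.4%
   - Δ = 1.24: Φ(−0.73), about 23%
   - Δ = 0.84: Φ(−0.22), about 41%

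5. **What the stated H2 rule would do.** In a simple two-arm approximation, the chance of a non-significant difference (1 − power) is about 20% at a true deficit of 2.2 and about 71% at 1.1, provided both arms also improve.

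6. **A smaller margin at the same size.** Half of 2.20 is 1.10. Power = Φ(1.10/0.783 − 1.96) = Φ(−0.555), about 0.29, against about 0.80 at 2.20. A pass at 1.10 needs an observed difference below 1.10 − 1.53 = −0.43, that is, G4H observed at least 0.43 points better than CBT. For 0.80 power at 1.10, 267 per arm must be retained, or 267 / 0.67 = 399 randomised per arm.

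**The case against.** The strongest reply is that a confidence-limit rule is stricter than the margin looks. With 67 per arm, the observed deficit could be at most 0.67 points, so about 70% of the estimated CBT effect would be kept in the point estimate. If CBT's effect really is 2.22, a G4H equal to control would pass only about 2.4% of the time. That stands. A reader might infer that a limit just under 2.20 never rules out loss of all of CBT's benefit. On the protocol's own point estimate it does rule that out, barely. The risk comes from CBT's true effect being smaller than 0.49. However, the protocol does not state a confidence-limit rule, so this protection is not currently in the plan.

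Other points deserve weight:

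- **The control.** The CBT program was shown effective "in a sample of high-risk adolescents relative to active control groups". Being no better than that control is not the same as having no benefit. The article gives no effect over no treatment and does not argue from one.
- **Clinical relevance.** The outcome section treats improvement above 3 points as clinically significant, and 2.20 lies below that. The article does not connect the two, and a loss of 2.20 would still remove nearly all of CBT's estimated advantage.
- **Timing.** A reader might infer that a 6-month effect makes the margin too loose for H2 at program completion. The documents do not show this. The Background says that treatments generally relieve acute symptoms but prevent relapse poorly, which points, if anywhere, to a larger effect at completion.
- **Transfer to this trial.** CBT is delivered "with minor adaptations to ensure comparable structure and amount of face-to-face contact as the G4H condition", and entry is possible on loneliness alone. Neither fact comes with a size or direction for the CBT effect, so neither is relied on here.
- **The 1.8 to 2.6 multiple.** It rests wholly on assumed arm sizes and is illustrative.

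**Conclusion.** The concern holds in this form. The margin is 99% of the protocol's own estimate of CBT versus control, preserves about 0% of the comparator's benefit, and ignores that estimate's uncertainty. This follows from the document's figures alone. Meeting 2.20 would show at most that some of CBT's estimated effect is kept, which does not support H2 as worded. The stated decision rule does not test against the margin in any case.

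That G4H could pass while no better than the historical control is conditional on CBT's true effect being smaller than 0.49. The illustrative chances of 23% to 41% assume that the true effect sits at the lower limit computed for two to four equal arms. The sample size arithmetic itself is correct for the margin chosen.

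**What to change.** Keep N = 200 and revise the sample size and Analyses sections as follows.

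1. Judge H2 by the 95% confidence interval for the G4H minus CBT difference in depression from the planned mixed model, in place of the non-significant interaction.
2. State that an upper limit below 2.20 supports only the claim that G4H has not lost all of CBT's estimated effect, and so is indirectly better than the historical control.
3. Reserve non-inferiority to CBT, or equal effectiveness, for a smaller margin tested next in fixed sequence on the same interval. This costs no alpha.
4. Justify that smaller margin by a preserved fraction and by the lower confidence limit of the historical effect, which the sponsor can compute from its source. Half the effect, 1.10, is an illustration only: it exceeds the lower limit computed for three or four arms (1.03 and 0.84 points), and the margin should be lower if the actual limit is lower.
5. State the power of each step: before clustering and with 67 per arm, about 0.80 at 2.20 and about 0.29 at 1.10.

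The change is to wording and to the decision rule, with no added participants. The real cost is that the stronger claim becomes harder to reach and its stated power is low. Powering the trial fully for 1.10 would need about 399 randomised per arm, so restricting the claim is the practical route.

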## Method

### Trial design

CARR is a two-arm non-inferiority parallel (1:1 ratio) randomised controlled trial. A summary of this study’s compliance with Standard Protocol Items: Recommendations for Interventional Trials (SPIRIT), is provided in the Additional file 1.

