### Randomisation

Participants who are eligible will be randomly assigned by the research team following simple randomisation procedures (computerized random numbers using Excel random number generator feature) to either G4H or CBT using a 1:1 ratio. Participants will be randomised at the group level once sufficient participants have been recruited for a group (minimum of 5). That is, participants will first be recruited into a treatment group, and each group will then be randomised to receive either G4H or CBT, using the randomisation process outlined above. Neither the participant nor the research team will be blind to intervention status. Assessment of primary outcomes at each timepoint will occur via a web interface to ensure that this is not affected by intervention status.

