### Analyses

Data quality will be improved by using a web interface that prompts (but does not force) participants to complete missing items. This will reduce missing data and prevent errors from manual data entry. Data quality will be checked by assessing ranges for each variable and interrogating outliers. We will examine the differences in baseline characteristics between the groups descriptively. Since differences between randomised groups at baseline could have occurred by chance, no formal significance testing will be conducted (in accordance with recommendations by [50]). No covariates will be included in the primary analysis (in accordance with recommendations by [51]). However, we will include exploratory analyses which assess the interaction between condition and baseline characteristics where indicated.

To assess the effect of intervention, group differences on the primary and secondary outcome measures, with all available timepoints included in the model, will be examined using a series of mixed effects repeated measures (MMRM) models, which will specify timepoint, participant, and therapy group as levels in the analyses. MMRM is a full information maximisation likelihood estimation strategy that can model data even when some observations are missing, and thus honours the intention-to-treat principle [52]. For all hypothesis testing, both intention-to-treat analyses (ITT; where all available data are included in MMRM) and per protocol analyses (PP; only including participants who met eligibility criteria throughout the trial period, were randomly assigned, completed the intervention according to the protocol, and had both baseline and follow up data) will be completed. Best fit, as determined by Information Criteria (e.g. AIC; BIC) method will be used for determining the covariance structure for MMRM models.

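### The 67 retained per condition carry no allowance for clustering, although whole therapy groups are randomised, so the stated 0.80 power does not describe this design

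*Protocol article*

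**What the plan says.** Under Sample size power calculations, the protocol article takes a historical effect of CBT against control, d = "0.49 at 6 month follow up", and converts it to points: "This corresponds to 2.2 points on the DASS-21 depression subscale", using a standard deviation of 4.53. It continues "To have 0.80 power to detect this difference with an alpha level of 0.05" and concludes that "67 people per condition would need to be retained at follow up". The only further adjustments are 50% eligibility and 67% retention, which take 400 screened to 200 enrolled and 67 per condition at follow-up.

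Under Randomisation, the unit of allocation is the therapy group: "Participants will be randomised at the group level once sufficient participants have been recruited for a group (minimum of 5". The Intervention section sets the range at 5 to 9 people per group, with two facilitators for each. Under Analyses, the mixed models are ones "which will specify timepoint, participant, and therapy group as levels in the analyses".

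**The concern.** When intact groups are randomised and then treated together, outcomes within a group tend to be correlated. Each participant then carries less independent information than in an individually randomised trial, and the treatment contrast is judged against variation between groups, of which there are few. The planned analysis recognises this by including therapy group as a level. The sample size calculation does not, so the two sections assume different designs.

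The document itself gives reason to expect some correlation: G4H is described as working partly through identification with the therapy group, and group identification and cohesion are process measures.

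At stake is the power claim for the non-inferiority comparison on depression, with its margin of 2.20 points. A wider interval than planned makes it more likely that a truly non-inferior G4H fails to show non-inferiority.

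**Working it through.** **Inputs from the protocol article.** d = 0.49; 2.2 points; SD 4.53; power 0.80; alpha 0.05 (sidedness not stated); 67 retained per arm; 200 enrolled (100 per arm); 67% retention; 5 to 9 people per group.

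**Assumed, not in the document.** ICC 0.02 to 0.10, with 0.01 shown as a low case; equal group sizes; the same 67% retention in every group.

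**1. Reproducing the plan's figure.**
- Conversion: 0.49 × 4.53 = 2.22, given as 2.2.
- Two-sample t test, d = 0.49, two-sided 0.05, power 0.80: n = 66.4 per arm, rounded up to 67. Power at 67 is 0.804.
- Normal formula with the raw values: n = 2 × (1.960 + 0.842)² × 4.53² / 2.2² = 66.6, again 67.
- One-sided 0.05 gives 53 to 54 per arm, which does not match.

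So 67 is the individually randomised figure with no term for clustering.

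**2. Is there a reserve?** 400 × 0.50 = 200 enrolled; 200 × 0.67 = 134 = 2 × 67. None, apart from rounding 66.4 up to 67 (67 / 66.4 = 1.009).

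**3. Adding clustering.**
- Retained group size: m = 5 × 0.67 = 3.35 up to 9 × 0.67 = 6.03.
- Design effect: DE = 1 + (m − 1) × ICC.
- Effective sample size per arm: 67 / DE.
- Groups per arm: k = 100 / 5 = 20 down to 100 / 9 = 11.1.
- Group-based degrees of freedom: 2k − 2, that is 38 down to about 20.
- Power: non-central t with non-centrality 0.49 × √(effective n / 2), two-sided 0.05.

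| Recruited per group | m | ICC | DE | Effective n per arm | Power, design effect only | Power, group-based df |
|---|---|---|---|---|---|---|
| 5 | 3.35 | 0.01 | 1.02 | 65.5 | 0.79 | 0.78 |
| 5 | 3.35 | 0.02 | 1.05 | 64.0 | 0.79 | 0.77 |
| 5 | 3.35 | 0.05 | 1.12 | 60.0 | 0.76 | 0.74 |
| 5 | 3.35 | 0.10 | 1.24 | 54.3 | 0.72 | 0.70 |
| 9 | 6.03 | 0.01 | 1.05 | 63.8 | 0.78 | 0.75 |
| 9 | 6.03 | 0.02 | 1.10 | 60.9 | 0.76 | 0.73 |
| 9 | 6.03 | 0.05 | 1.25 | 53.5 | 0.71 | 0.67 |
| 9 | 6.03 | 0.10 | 1.50 | 44.6 | 0.63 | 0.60 |

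Groups of 7 lie between: 0.75, 0.71 and 0.65 with group-based degrees of freedom at ICC 0.02, 0.05 and 0.10.

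**4. Degrees of freedom alone.** At ICC 0, basing the test on the number of groups gives 0.79 (groups of 5) to 0.77 (groups of 9), already below 0.80.

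**5. Sensitivity to the effect size used.** With 2.2 / 4.53 = 0.486 in place of 0.49, the group-based results are about one percentage point lower (0.76 to 0.59 over ICC 0.02 to 0.10).

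**The case against.** *The size rests on inputs the document does not give.* This stands. The ICC is assumed, group size is known only as a range, and part of the loss comes from the choice of degrees of freedom. With small groups and an ICC near 0.01 the design-effect loss is minor. The omission is certain; a material loss is not certain over the whole plausible range.

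*Retention is called conservative because follow-up incentives were added.* It is, but no surplus is quantified or offered against clustering, and the power statement is tied to 67 retained whatever the retention turns out to be. If retention were 80% (an assumption), 80 per arm would remain. Groups of 5 at ICC 0.02 (m = 4, DE = 1.06, effective n 75.5) would then give 0.835 with group-based degrees of freedom. Groups of 9 at ICC 0.10 (m = 7.2, DE = 1.62, effective n 49.4) would give 0.640. Better retention could rescue the favourable cases, not the others.

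*Alpha may be one-sided, or repeated measures may add precision.* At one-sided 0.05, 53 per arm would suffice and 67 would absorb a design effect of 67 / 53 = 1.26. But 67 is not the one-sided result, so that is not the calculation made. The calculation also takes no credit for repeated measures: it uses the raw standard deviation.

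*An article condenses.* True of detail, but here a definite sample size and power are stated, and they reproduce only without a cluster term. A later analysis plan would not make that statement correct.

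Two stronger readings are tempting. A reader might infer that the analysis will ignore clustering of change and so inflate the type I error. The Analyses section names therapy group as a level and does not say how it enters; the form of the random effect and small-sample degrees of freedom may properly be settled in the analysis plan. A reader might also infer that the Trial design section misrepresents the design, since it says only that "CARR is a two-arm non-inferiority parallel (1:1 ratio) randomised controlled trial". The Randomisation section discloses group allocation openly, so this is a matter of labelling.

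**Conclusion.** The point holds as an omission in the power calculation. The arithmetic is correct for an individually randomised trial, which this is not. With group-based degrees of freedom, 67 per arm falls short of 0.80 at every ICC, including zero. From the design effect alone, any ICC beyond the trivial slack left by rounding does the same.

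Under the assumed ICC of 0.02 to 0.10, with 67% retention and groups of 5 to 9, power is about 0.79 to 0.63 from the design effect (1.05 to 1.50) and about 0.77 to 0.60 with group-based degrees of freedom. The document does not support a single figure within that range, nor a claim that the trial is badly underpowered whatever the ICC.

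**What to change.** In Sample size power calculations, state an assumed ICC with its source, the mean retained group size and the expected number of groups per arm. Apply 1 + (m − 1) × ICC with degrees of freedom based on the number of groups, and replace the unqualified 0.80 with the resulting power over a range of ICC and over group sizes of 5 to 9. The ICC should be the investigators' own choice; the values used here are illustrative.

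This changes wording only. It needs no extra enrolment, and its cost is a less favourable stated power. Keeping 0.80 instead would require more participants: at ICC 0.05 the design effect alone takes 67 to 67 × 1.12 = 75 up to 67 × 1.25 = 84 retained per arm, before any allowance for group-based degrees of freedom.
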